In addition, we defined a graded framework for AE seriousness and relatedness to guide session management:-Mild AE: No session suspension required. Symptoms are transient and resolve without intervention (e.g., mild and temporary facial pallor without changes in vital signs);-Moderate AE: Interruption of a single session is required. Symptoms resolve within the same day (e.g., oxygen desaturation resolving after endotracheal suctioning);-Severe AE: Permanent discontinuation of treatment is considered in case of repeated or persistent AE unresponsive to intervention (e.g., hypotension not responding to reduction in tilt angle), or based on medical judgment prioritizing patient safety.

AEs will be managed according to the 90/385/EEC and 93/42/EEC regulations.

A concomitant usual care and rehabilitation interventions will continue without restriction for both arms. Regardless of allocation to the VEM or TV group, all patients will carry out the comprehensive rehabilitation program as designed by the participating center for the entire study period. The usual rehabilitation program consists of alternating bed positioning, passive limb mobilization, cognitive training, activities to facilitate recovery of consciousness (e.g., multisensorial stimulation), speech, and swallowing therapy. During VEM in sABI study, clinicians will be asked to exercise caution when prescribing “prohibited” (i.e., not permitted under the study protocol) and “proscribed” medications (i.e., permitted but requiring careful documentation and, when necessary, adjustment in timing or dosage). These medications may compromise safety (prohibited agents associated with orthostatic hypotension), and affect the interpretability of outcomes by influencing cognition, attention, arousal, or consciousness (proscribed medications) [21,22]. A list of contra-indicated medications and/or cautions is reported in the Appendix B. Information on pharmacological treatments will be collected at baseline and at all follow-up time points.

At the end of the fifth week of treatment (T1), and after 1 month from T1 (T2) a clinical–functional and neurophysiological evaluation will be performed. A serum blood sample will be collected at T2 (see Table 3).

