### 2.6. Statistical Plan

All analyses will be conducted by blinded statisticians. Frequencies (percentages) or mean ± standard deviation will be used for descriptive statistics regarding socio-demographic and clinical variables, as well as for the level of satisfaction with the experimental intervention and the occurrence of side effects.

Given that most outcomes are ordinal or exhibit skewed distributions, we will employ linear or generalized linear mixed-effects models (LMM/GLMM) with appropriate link functions. Ordinal outcomes will be analyzed using cumulative logit mixed-effects models, with random intercepts for patients and for enrolling centers. Continuous outcomes approximately normally distributed will be analyzed with LMM, while skewed continuous outcomes will be modeled with appropriate link functions (e.g., log). All models will adjust for baseline values of the outcome (ANCOVA framework) and include time (T0, T1, T2) and group (VEM, TV) as fixed effects, plus their interaction. Model formulas were defined a priori. The following is an example:logit[P(Y_ij_ ≤ k)] = β_0_ + β_1_Group_i_ + β_2_Time_j_ + β_3_Baseline_i_ + β_4_(Group_i_ × Time_j_) + u_patient(i)_ + u_center(i)_
where u_patient(i)_ and u_center(i)_ are random intercepts for patient and center, respectively.

All analyses will be performed with a two-sided significance level of 0.05. Adjustment for multiple comparisons will be made using Benjamini–Hochberg false discovery rate correction. Statistical analyses will be conducted using R (version 4.4.3; R Foundation for Statistical Computing, Vienna, Austria) or equivalent statistical software. Interim analyses are planned at half of the expected sample for safety outcomes only (i.e., AEs).

Patients violating the VEM-sABI protocol will be excluded from the VEM or TV treatment, but the last clinical observation will be considered for statistical analysis, according to an intention-to-treat approach and a Missing at Random (MAR) assumption inherent to the mixed-model framework. To explore the robustness of the results in scenarios where data may be Missing Not At Random (MNAR), we will conduct pre-specified sensitivity analyses using multiple imputation and, where appropriate, alternative approaches such as joint modeling or delta-adjusted pattern-mixture models.

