Protocol violations include: ex-novo administration or change in dose of proscribed drugs (see list in Appendix B), occurrence of severe AE, transfer to acute wards due to severe medical complications, futility of the intervention (as the patient regains the ability to maintain a 90° upright position for ≥15 min without signs of hemodynamic instability on two consecutive days, combined with functional trunk and lower limb control as reflected by a score of ≥3 in the mBI sub-items “Ambulation”, i.e., constant presence of one or more assistants is required during ambulation, and ≥5 in the sub-item “Stair climbing”, i.e., the patient is able to ascend/descend but is unable to carry walking aids and needs supervision and assistance), missing two consecutive sessions or more than five total sessions or request from patients or their legal representative to withdraw from the study.

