These “Proscribed” medications are all drugs that may influence cognitive status, attention, arousal, or level of consciousness. These pharmacological effects can significantly bias the assessment of cognition and reduce the validity of intervention primary outcomes. These medications not necessarily need to be discontinued before the intervention, but must be carefully documented (“recorded”) in the study records (on REDCap registry), and may require adjustments (“adjusted”) in timing or administration according to clinical condition and safety (e.g., give in the evening after intervention or clinical-EEG assessment instead of morning, temporarily reduce dose, etc.), to avoid interference with primary outcomes (e.g., alertness, cognitive performance). If the patient is under one of these drugs at study entry, the patients are eligible if they keep the same dosage during the study protocol. If the dosage changes, or one of these drugs needs to be started or discontinued, this is considered as a protocol violation.

The following Table A3 provides a comprehensive overview of CNS-active drugs that may negatively impact cognitive performance [22,49]. It includes their expected cognitive effects, approximate half-lives, and recommended timing for possible tapering or discontinuation before the intervention onset. These recommendations are based on pharmacokinetics (typically 4× half-life for elimination of clinical effect) and clinical safety considerations.

Table A4 summarizes both pharmacological and non-pharmacological interventions that have been proposed to enhance recovery of consciousness and cognitive functioning in patients with severe brain injury, as outlined by Edlow et al. [21]. While a limited number of interventions (such as amantadine and transcranial electrical stimulation) are supported by moderate-to-high level evidence from RCTs, the majority remain experimental, supported only by preliminary data (e.g., case reports, early-phase trials).

**Table A3 jcm-14-06628-t0A3:** Proscribed medications negatively impacting cognitive performance.

Drug Class	Examples	Half-Life (approx.)	Cognitive/CNS Effects	When to Stop Before Cognitive Tasks/Intervention
Z-drugs	Zolpidem	2–3 h	Memory alteration, confusion	12–24 h before
Typical Antipsychotics	Haloperidol	14–26 h	Rigidity, slowed cognition, delirium	≥3–4 days before

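### A dose reduction of a proscribed drug is both allowed and a violation that ends VEM or TV, and several Table A2 hold times fall below the stated four half-life minimum

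*Protocol article*

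**What the plan says.** **Proscribed drugs (CNS-active; Appendix B, Tables A3 and A4).** Section 2.3.2 opens its medication paragraph with "During VEM in sABI study, clinicians will be asked to exercise caution when prescribing" and then defines this group as "permitted but requiring careful documentation and, when necessary, adjustment in timing or dosage". Appendix B gives examples of such adjustments: "give in the evening after intervention or clinical-EEG assessment instead of morning, temporarily reduce dose, etc". A few lines later it says that "the patients are eligible if they keep the same dosage during the study protocol", and then: "If the dosage changes, or one of these drugs needs to be started or discontinued, this is considered as a protocol violation". The list of violations in section 2.6 includes "ex-novo administration or change in dose of proscribed drugs". The same section says that violators "will be excluded from the VEM or TV treatment, but the last clinical observation will be considered for statistical analysis". It describes this handling of their data as being "according to an intention-to-treat approach and a Missing at Random (MAR) assumption inherent to the mixed-model framework".

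**Prohibited drugs (risk of orthostatic hypotension; Appendix B, Table A2).** The text above the table requires at least four half-lives between stopping such a drug and enrolment, and it forbids starting one between T0 and T2. Table 2 makes the presence of a prohibited drug an exclusion criterion. Table A2 then lists, for each class, an estimated half-life and a recommended action, in most rows a hold time in hours. For beta-blockers the action offers a dose reduction as an alternative to a 24 h hold.

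**The concern.** The first problem is that one act falls under two rules. A clinician who lowers a sedating drug for a few days, to protect alertness at treatment or assessment, is following section 2.3.2 and Appendix B. Under the next sentences of Appendix B and under section 2.6, the same clinician has created a violation, and the patient stops VEM or TV. The treating clinicians know the allocation (section 2.3.1), and six centers must each decide which rule applies.

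The second problem is that Table A2 gives sites hold times that do not meet the rule printed above it. These drugs are listed because they may make tilting unsafe. A site that works from the action column would stop some of them later than the protocol's own minimum allows.

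**Working it through.** **1. The dose rule, side by side**

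| Act on study | Section 2.3.2 / Appendix B examples | Appendix B rule / section 2.6 |
|---|---|---|
| Move a dose to another time of day | allowed | not listed as a violation |
| Temporarily reduce a dose | allowed | violation; VEM or TV ends |
| Start a proscribed drug | – | violation; VEM or TV ends |

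Only the second row conflicts. Could the allowed reduction be meant for the time before entry only? Section 2.3.2 places its instruction during the study. The companion example in Appendix B moves a dose to after the intervention or the EEG assessment, which are on-study events. A temporary reduction also implies a later return to the old dose. It would escape the violation rule only if the study fell wholly between the reduction and the return, and no such limit is stated.

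Sessions lost when a patient is removed after week *w*: 25 − 5*w*. For *w* = 1, 2, 3, 4 this gives 20, 15, 10, 5 sessions, or 80, 60, 40, 20% of the course. The article gives no rate of dose changes, so this cannot be turned into a number of patients.

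**2. Table A2 against four half-lives**

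Inputs: the half-life and hold time printed in each row. Required washout = 4 × half-life. Fraction of drug left = 0.5^(hold / half-life), assuming simple first-order elimination. Four half-lives leave 0.5⁴ = 6%.

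| Drug or class | Half-life (h) | 4 × half-life (h) | Hold in table (h) | Left after hold |
|---|---|---|---|---|
| *Short outright* | | | | |
| Alpha-blockers | about 22 | 88 | 48 | 22% |
| Tricyclics | 25 | 100 | 48–72 | 26–14% |
| Diazepam | >30 | >120 | 24–72 | at least 57–19% |
| *Short at the upper listed value* | | | | |
| Atenolol | up to 24 | up to 96 | 24 | 50% |
| Metoprolol | 1–9 | 4–36 | 24 | 16% |
| ACE inhibitors | 11–24 | 44–96 | 24–48 | 50–25% |
| ARBs | up to 24 | up to 96 | 24–48 | 50–25% |
| Antipsychotics | 3–30 | 12–120 | 48 | 33% |

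For the second group, the last column uses the upper half-life. At the lower listed half-life, metoprolol (4 h) and antipsychotics (12 h) comply, and so do ACE inhibitors if held for 48 h (44 h needed).

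Rows at the margin:
- Furosemide in renal failure falls short: 12–24 h against up to 96 h.
- Oxycodone falls short: 24–48 h against more than 48 h.
- Lorazepam needs 48–64 h, which the 72 h end of its range meets and the 24 h end does not.

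Rows that comply:
- Furosemide with normal renal function: 12–24 h against 4–6 h.
- Nitrates: the day before, taken as 24 h, against 4–20 h.
- Morphine: 24–48 h against 8–16 h.

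The dopaminergic row gives no time and cannot be tested.

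**The case against.** **On the dose rule.** The violations in section 2.6 are partly a list of stopping events. It includes severe adverse events, transfer to acute care, and recovery of upright posture, none of which is misconduct. On that usage an allowed act may still end treatment. This is a fair reading of the list, but it does not remove the conflict. The adjustment is offered as a way to protect the outcome assessment, and eligibility is tied to an unchanged dose. An instruction to adjust the dose makes no sense if following it ends the patient's treatment. It is also fair that the violation sentence is explicit, that it agrees with section 2.6, and that monthly calls with all centers make divergent practice less likely. These points show which rule should survive; they do not repair the text.

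**On Table A2.** The four half-life minimum and the exclusion criterion are binding, while the table column is only a recommendation, hedged in several rows. That stands. A reader might infer that patients will be tilted with the residual levels shown above. The documents do not support this. The minimum governs entry, the table times have no stated reference point, and sessions start only after T0, which may be up to a week after enrolment. Counting the holds back from each session does not rescue the table, because that would imply continued use of drugs that are prohibited from T0 to T2. The dose-reduction option for beta-blockers can be read as the taper that Appendix B allows before enrolment. It is unclear rather than plainly contradictory.

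**On consequences for the analysis.** A reader might infer that removal feeds a carried-forward LCF value into the primary analysis. Section 2.6 can equally mean that data up to removal enter a mixed model under MAR, so no such claim is made here.

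**Conclusion.** Both points hold and should be corrected. The first is a conflict in the wording: reducing the dose of a proscribed drug during the study is allowed and is also a violation that ends randomized treatment. Changes of timing alone are not affected. For an affected patient the cost is 20 to 80% of the sessions if removal falls at the end of weeks 1 to 4. How often this would happen is unknown.

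The second is a table that recommends less than the protocol's own minimum. The shortfall is outright in three places and depends on taking the upper listed half-life in five more. It rests on the half-lives as printed and on reading the hold times as serving the same purpose as the stated washout. It does not extend to every row.

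Three overlaps are editorial only: amitriptyline appears in Tables A2 and A4; midazolam (Table A4) belongs to a class that Table A2 prohibits; and section 2.4.2 uses benzodiazepines as its example for EEG timing. No effect on power, bias or the primary estimate is shown for any of this.

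**What to change.** **Proscribed drugs.** In section 2.3.2, remove dosage from the definition so that only timing may be adjusted. In Appendix B, delete the temporary-reduction example. Add one sentence: any dose change must be made and stable before T0; after T0 the timing may shift but the dose may not. The alternative, exempting documented dose reductions from the violation rule, would keep more patients on treatment but would let changes in CNS-active drugs coincide with the LCF assessment. That is a trade-off for the sponsor and is not needed to remove the conflict.

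**Table A2.** Set the holds to at least four half-lives before enrolment:
- alpha-blockers: 88 h
- tricyclics: 100 h
- diazepam: more than 120 h
- atenolol, ACE inhibitors and ARBs: up to 96 h
- metoprolol: up to 36 h
- antipsychotics: up to 120 h, by drug

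For beta-blockers, replace the present action with taper and stop before enrolment. The marginal rows (furosemide in renal failure, oxycodone, the short end for lorazepam) and the three overlaps can be tidied in the same edit.

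**Cost.** A text amendment, with no new visits or data. Some patients would wait slightly longer before entry than the table now suggests, for example 88 − 48 = 40 h more for alpha-blockers. A site that already applies the stated minimum would see no change.

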### 2.4. Outcome Measures

Almost all measures will be collected at study entry (T0) and at T1 and T2 to evaluate the (possible) changes in the two follow-ups with respect to T0. Primary, secondary, and exploratory outcomes and related measures are summarized in Table 3.

The clinical–functional evaluation includes the following:-The Level of Cognitive Functioning (LCF) [24,25], an observer-rated scale (from coma to purposeful appropriate behavior) divided into eight levels that describe the patterns or stages of recovery typically seen after a brain injury.-The Coma Recovery Scale-Revised (CRS-R) [23,26] is an observer-rated tool designed to assess patients with disorders of consciousness. It evaluates auditory, visual, motor, oromotor/verbal, communication, and arousal functions to help differentiate between vegetative state, minimally conscious state, and emergence from these conditions.-The Disability Rating Scale (DRS) [27], an observer-rated, 30-point continuous scale that provides quantitative information to document the progress of patients with severe brain injury from coma to community reintegration. It evaluates 8 areas of functioning, organized into 4 categories: (1) consciousness (eye opening, verbal response, motor response); (2) cognitive ability (feeding, toileting, grooming); (3) dependence on others; (4) employability. Each area of functioning is rated on a scale of 0 to either 3, 4, or 5 (maximum score = 30-death, minimum score = 0-person without disability) with the highest scores representing the higher level of disability.-The Modified Ashworth Scale (MAS) [28], an observer-rated scale used to measure muscle spasticity by assessing resistance during passive soft-tissue stretching. Scores range from 0 (no increase in muscle tone) to 4 (rigid in flexion or extension).-The Medical Research Council (MRC) scale [29], an observer-rated scale for assessing muscle strength, scoring from 0 (no contraction) to 5 (normal strength) in specific muscle groups.-The Fondazione Don Gnocchi Clinical Complication Scale (FDG-CCS) [30], an observer-rated tool for recording and grading clinical complications during rehabilitation of patients with sABI, covering medical, nursing, and functional events to support patient monitoring and care planning.-The modified Barthel Index (mBI) [31], an observer-rated continuous scale for evaluation of ability to perform autonomously personal activities of daily living. It measures physical disability across 10 categories that are scored from 0 to either 5, 10, or 15 (maximum score = 100-independence, minimum score = 0-complete dependence) with the highest scores representing the higher level of independence.-The System Usability Scale (SUS) [32] is a simple, ten-item 5-point Likert scale giving a global view of subjective assessments of usability, including effectiveness, efficiency, and satisfaction of a device. Higher scores correspond to higher usability.-The Nociception Coma Scale–Revised (NCS-R) [33], an observer-rated tool to assess pain-related behaviors in patients with disorders of consciousness. It evaluates motor, verbal, and facial responses to noxious stimulation, with higher scores indicating stronger nociceptive responses. -The Agitated Behaviour Scale (ABS) [34], an observer-rated scale measuring the nature and extent of agitation during recovery from brain injury. It assesses behavioral, emotional, and cognitive components, with higher scores indicating greater agitation severity.

#### 2.4.1. Blood Biomarkers and Sampling Procedure

Three blood biomarkers will be collected, as they have been correlated to neuronal degeneration and plasticity in patients with sABI and pDoC [35]: (i) Brain-Derived Neurotrophic Factor (BDNF), a neurotrophin involved in neurogenesis and synaptic plasticity, which can be upregulated by physical exercise [36]; (ii) Neurofilament Light chain (NF-L), a marker of primary and secondary neurodegeneration in sABI previously linked to long-term axonal degeneration and poor outcome [37]; and (iii) Glial Fibrillary Acid Protein (GFAP), a filament protein that has been found to be related to brain function recovery [38].

For each patient, two blood samples (2 × 6 mL vacutainer tubes) will be collected in the morning following an overnight fast, according to a standardized procedure. Each sample will be labeled with a unique reference ID code. Serum will be obtained by centrifugation at 3000 rpm for 15 min and divided into four 500-microliter aliquots. Serum samples will initially be stored at −20 °C at the enrolling centers for a short period prior to shipment, due to the unavailability of −80 °C storage facilities at the participating clinical sites. Shipments will occur promptly, and upon arrival at the central analysis laboratory, all samples will be immediately transferred to −80 °C for long-term storage. BDNF, NF-L, and GFAP in serum will then be analyzed using the Ella Automated Immunoassay System (Bio-Techne, Minneapolis, MN, USA). Sample collection, storage, and shipment will be performed in accordance with established standard operating procedures, ensuring consistency, traceability, and compliance with best laboratory practices.

#### 2.4.2. EEG Recording and Analysis

EEG recordings will be performed at T0, T1 (post-treatment), and T2, which will evaluate changes in cortical electrophysiological activity that may occur even in the absence of overt clinical improvements in some patients [39]. The neurophysiological assessment will include two consecutive eyes-closed (forced for pDoc patients) EEG recordings:“resting-state” EEG (duration 15 min).“reactivity” EEG (duration 15–17 min) using the following randomized stimuli (each stimulus twice; interstimulus interval ≥ 1 min):eye opening and (forced) eye closing;proximal noxious stimulation (deep pressure applied to the trapezius muscle on each side);distal noxious stimulation (pressing fingernail beds on each hand);acoustic stimulation (hand clapping);personalized acoustic stimulation (patient’s name);intermittent photic stimulation (5 s trains of flashes at 1-2-8-10-15-18-20-25-40-50-60 Hz)

EEG will be recorded by means of 19 electrodes placed on the patients’ scalp according to the international 10–20 system (Fp1, Fp2, F7, F8, F3, F4, C3, C4, T3, T4, P3, P4, T5, T6, O1, O2, Fz, Cz, Pz) plus electrooculogram and electrocardiogram. Data will be sampled at a minimum of 512 Hzand with hardware LP-HP filters open; a notch filter will be used to eliminate frequencies around 50 Hz for online visualization. EEG recordings will take place with the patient sitting on her/his wheelchair, in morning time after customary nursing procedures and (at least) 10 h after administration of drugs acting on the central nervous system, such as myorelaxants and sedative drugs (e.g., benzodiazepines) to optimize vigilance.

The EEG will be analyzed by means of both qualitative (i.e., visual analysis of EEG background activity and reactivity) and quantitative (e.g., power spectrum, microstate, and connectivity analysis) procedures. Specifically for the qualitative analysis, EEG background activity will be classified into five severity categories, according to recently proposed criteria for patients with sABI and the standardized classification of EEG features [40,41].

